#### Clinical Significance

The clinical significance of an improvement in outcomes in response to treatment for pediatric sleep problems has not been defined. Various methods have been used to examine clinical significance [117,118]. Minimal important difference (MID) is an important metric of clinical significance. The MID refers to “the smallest difference in score in the domain of interest which patients perceive as beneficial and which would mandate, in the absence of troublesome side effects and excessive cost, a change in the patient’s (health care) management” [119]. The MID has not been determined for most pediatric health issues utilizing parent-reported outcomes [120]. We will examine clinical significance in 2 ways for both of the primary outcomes. First, the reliable change index (RCI) will be computed and the percentage of cases that exceeded RCI>1.96 will be determined [121]. The RCI is a distribution-based metric that informs the extent to which an observed change is reliable; it is often used in mental-health treatment studies [122,123]. Second, at baseline, all participants are asked to rate the “smallest amount of improvement” on their child’s sleep problems that they would be satisfied with, using a 10 cm visual analog scale (not at all improved, 0%; completely improved, 100%). The average is used as a method of estimating the MID [124] and has been used in other pediatric sleep intervention trials [125]. The percentage of cases that achieve at least this level of improvement between baseline and either 4 months or 8 months postrandomization will be computed.

## Results

The RCT for the English language population was launched in September 2016 and the expected date of completion is February 2018. The RCT of the French language population was launched in May 2017 and is expected to be completed in February 2018. Data analysis will be completed by 2019.

## Discussion

### Main Goals

Our primary purpose for this study is to provide a readily accessible, evidence-based eHealth intervention to increase access to care for insomnia in typically developing children aged 1 to 10 years. With the significant percentage of the Canadian population with internet access [126], eHealth delivery has the capacity to be a powerful tool to overcome traditional systemic barriers to treatment access. The internet-based BNBD program similarly has the potential to (1) be integrated within a stepped-care model of pediatric services, (2) improve parents’ knowledge about behavioral treatments for insomnia, (3) improve accessibility of treatment interventions for children and their families, and (4) reduce service demands at the frontline of clinical practice.

### Ethical Considerations

#### Informed Consent

Ethics approval was granted by IWK Health Centre Research Ethics Board. To ensure informed consent, participants must sign the internet-based screening information and consent form and the information and consent form after the nature of the study has been fully explained. Participants are not able to proceed to any study-related activity before electronically signing consent. These consent forms inform participants that participation is voluntary and that they may withdraw consent to participate at any time, and they are informed of the aims, methods, benefits, and risks of the study. All participants are given an opportunity to contact research staff by email or to request a phone call to have any questions answered and concerns addressed. A series of true and false questions to test participants’ knowledge of their research rights are used to ensure informed consent. A copy of both the screening information and consent form and the information and consent form are available to be downloaded and saved by participants. Participants provide an electronic signature and date and click an “I Agree” button.

#### Privacy, Personal Health Information, and Study Data

The study is conducted in accordance with all applicable standards and procedures of the IWK Health Centre, as well as the Personal Health Information Act, Personal Information International Disclosure Protection Act, and the Tri-Council Policy Statement: Ethical Conduct for Research Involving Humans.

Personal health information and study data that are collected, used, or disclosed are limited to those data that are necessary to fulfill the objectives of the study explained in this protocol, and all data are handled in a confidential manner. Study data are identified using a unique identifier code. A key file is used to link this identifier to participants’ email addresses. Data are not affiliated with any personal health information, and all data are collected and stored on the Canadian-based secure servers, the REDCap electronic data capture system and the Dalhousie University server. Identifying information is accessible only to the study investigators, postdoctoral fellow, and data management and research staff. All study data will be kept in a secure and confidential location for at least 5 years post data publication and then destroyed according to IWK Health Centre’s policy.

#### Safety Monitoring

This behavioral intervention involves minimal risk to the participants. Participants are provided with the email address of research staff whom they may contact in the event that they have concerns or questions related to the study. The study safety-monitoring plan involves communication between the research staff, who are in contact with participants, and the principal investigator (PVC), a registered psychologist. Any difficulties experienced by the participants that cannot be dealt with adequately by research staff are immediately communicated to the principal investigator or her delegate (coinvestigator) and follow-up with the participant is made to ensure their well-being. Data monitoring for adverse events or trends in outcome has not been undertaken given that this is a low-risk study. An adverse events committee, composed of the 3 members from Dalhousie University, not associated with the BNBD study, and having medical, psychology, and sleep expertise, will review adverse events if one becomes known during the course of the study.

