### Electronic Health (eHealth) Intervention

Participants randomized to the intervention group receive access to the BNBD intervention immediately, whereas participants randomized to the usual care condition receive access after they complete the 8-month follow-up assessment.

The BNBD intervention is fully self-guided (ie, there is no contact with coaches or clinicians), empowering parents to implement strategies independently. The program introduces evidence-based interventions, tailored content (ie, participants create personalized sleep routines, set individualized goals, and receive custom feedback on progress), and age-specific information delivered primarily through videos, supported by graphics, animations, and interactive elements to engage and encourage parents. Access to built-in tools and supports, such as sleep diaries and goal setting and tracking, provides feedback on participants’ progress.

The intervention includes 5 sessions made available sequentially to participants. Table 1 summarizes the content of the intervention. The recommended completion time of the intervention ranges from 5 to 10 weeks. Participants receive an automated email reminder when a session becomes available, a prompt to complete each session, and 7 notices that the recommended completion time is approaching. The core content is delivered primarily via videos and interactive activities to support the parents’ learning of these new skills.

Each session provides evidence-based information to parents, strategies for implementation of best practices to address sleep problems, and access to additional help and advice through a “Roadblock” question-and-answer style support detailing common obstacles to implementing the recommended interventional strategies and evidence-based methods to navigate these obstacles. There is also a “Reward Center” where parents can develop reward programs (eg, sticker charts) to help support the implementation of these sleep intervention strategies.

The program can be used at a time that is convenient for the participants, removing barriers to care and providing services in the comfort and privacy of their own homes. The intervention is hosted on the BeHealth Solution, LLC’s proprietary technology platform [68] and can be accessed through participants’ desktops, laptops, tablets, and mobile phones.

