Before beginning each session, starting with Session 2, participants are asked whether they wish to continue the intervention program. If participants indicate they are not interested in participating further, they are asked to complete a questionnaire and provide the reason, in an open-ended question, regarding why they no longer wish to continue the program.

**Table 1 table1:** Intervention sessions.

Session	Topic overview
Sleep information	Characteristics of sleep; types of sleep problems, sleep need; how sleep problems develop; impact and treatment of sleep problems
Healthy sleep practices	Daytime and bedtime routines; sleep hygiene/healthy sleep practices; sleep scheduling (including napping) and sleep routines
Independent settling at bedtime	Settling at bedtime; parents choose a sleep intervention that best fits their needs from 3 intervention strategies: controlled comforting, camping out, and bedtime fading
Night waking, napping, and early morning awakenings	Applying strategies to night waking; applying strategies to early morning awakenings; applying strategies to napping
Looking back and ahead	Relapse prevention; looking back at goals and progress; common pitfalls/roadblocks; what to expect at new developmental milestones; dealing with other sleep problems; making a plan

This allows participants the freedom to discontinue the program at any time and allows us to assess any issues that contributed to discontinuation. To allow for a process-level analysis, before starting each session, participants are also asked to complete the Insomnia Severity Index [69] scale and rate the sleep quality of their child to evaluate pediatric insomnia symptoms.

In addition, 2 measures are used to assess treatment fidelity. First, parents’ implementation of the intervention is assessed using process measures administered at the beginning of each session of the program. In advance of each subsequent module, participants are asked to record how carefully they reviewed the material, what percentage of the recommended strategies they implemented, and how successful they were in implementing these strategies, as well as to provide an estimate of the overall percentage improvement of their child’s sleep problems. Second, computer-generated user statistics captured by the intervention platform software are used to assess adherence, such as the number of times the site was accessed and the period of time taken to complete each module.

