#### Secondary Outcome Measures and Measures for Exploratory Analyses

Secondary outcomes and exploratory outcomes are assessed through the administration of internet-based questionnaires to assess children’s sleep and psychosocial health, parental function, treatment barriers, and predictors to successful intervention adherence. Each participant answers 13 to 15 questionnaires based on the group assignment (intervention or usual care) and age of the child.

All measures are available in both English and French, based on whether the participant has enrolled in the English or French language trial. All secondary and exploratory outcome measures are administered on the internet via REDCap. All electronic questionnaires underwent technical and usability testing by research staff and external reviewers, as well as by 6 parents of children ages 1-10 years. All questionnaires are displayed in a sequential manner. Certain measures are age-dependent, and REDCap automatically delivers them accordingly. All measures, and the time points that each is administered, are indicated in Table 2.

Please see Multimedia Appendix 1 for a detailed description of all measures used throughout the study.

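### Adverse events are captured only passively and with unequal chances to surface by arm, so reported counts would be neither comparable between arms nor evidence of safety

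*Protocol article*

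**What the plan says.** The Safety Monitoring section fixes how adverse events reach the trial. It states: "Data monitoring for adverse events or trends in outcome has not been undertaken given that this is a low-risk study". A committee of three people from outside the study "will review adverse events if one becomes known during the course of the study". Two routes are described. One is contact by the parent: "Participants are provided with the email address of research staff whom they may contact in the event that they have concerns or questions". The other is escalation by staff: "Any difficulties experienced by the participants that cannot be dealt with adequately by research staff are immediately communicated to the principal investigator".

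The section on secondary and exploratory measures says: "All measures, and the time points that each is administered, are indicated in Table 2". No row of Table 2 is an adverse event form or question.

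The section on the eHealth intervention adds contacts that exist in one arm only. "Before beginning each session, starting with Session 2, participants are asked whether they wish to continue the intervention program"; those who decline are asked for an open-ended reason. The stated purpose is: "This allows participants the freedom to discontinue the program at any time and allows us to assess any issues that contributed to discontinuation". The same arm also rates insomnia severity, sleep quality and implementation of the strategies around each session. Footnote b of Table 2 restricts the 4-month barriers and satisfaction scales to the intervention arm. The Randomization section says that participants are not blinded.

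**The concern.** A count of adverse events means something only if one knows who was asked and how. Here nobody is asked directly in either arm. What the committee sees depends on what happens to reach staff, in a trial where parents know their allocation and the two arms have different amounts of contact with the study.

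Two misreadings of the eventual report are then easy. A reader may take a count of zero as evidence that the programme is harmless, when it may only reflect that no one asked. Or a reader may compare counts by arm, when the chance that an event surfaces may differ between the arms for reasons unrelated to harm. Both matter because the programme runs without clinician contact and the protocol foresees commercial release if it proves effective.

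**Working it through.** The protocol states no adverse event rate, safety sample size or harm test, so there is no figure to reproduce. The check has three parts: an inventory of routes, and two illustrations in which the true risks and capture probabilities are my assumptions.

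**1. Routes by which a problem could surface**

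| Route | Intervention | Usual care | Asks about adverse effects? |
|---|---|---|---|
| Parent emails staff (Safety Monitoring) | yes | yes | no, unprompted |
| Staff contact with follow-up non-responders, 12 attempts (Follow-Up at 4 Months and 8 Months) | yes | yes | no |
| Continue/stop question with reason, before Sessions 2, 3, 4 and 5 | up to 4 times | none | no |
| Insomnia severity, sleep-quality and implementation ratings around sessions | yes | none | no |
| Barriers and satisfaction scales at 4 months (Table 2, footnote b) | yes | none | no |
| Child behaviour, teacher form, quality of life, sleep measures, parent depression/anxiety/stress, at baseline, 4 and 8 months (Table 2) | yes | yes | no, but deterioration in scores is measurable |

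No row solicits adverse effects. Three of the six rows exist in one arm only. The 4-versus-0 count of stopping questions is not an ascertainment ratio: the question concerns leaving a programme that usual care does not yet have, and nothing in the protocol sends the answers to the committee.

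**2. What zero reported events would show**

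Inputs: 500 enrolled, 1:1, so 250 per arm; 50% assumed lost (Sample Size Analysis), so 125 per arm.

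If true risk is p and the probability that an event is captured is c, the recorded risk is p × c. With zero events in n people the one-sided 95% upper bound on recorded risk is u = 1 − 0.05^(1/n), and the bound on true risk is u / c.

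- n = 125: u = 1 − 0.05^(1/125) = 0.0237
- n = 250: u = 1 − 0.05^(1/250) = 0.0119

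| n | c = 1 | c = 0.50 | c = 0.25 |
|---|---|---|---|
| 125 | 2.4% | 4.7% | 9.5% |
| 250 | 1.2% | 2.4% | 4.8% |

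Under passive capture c is unknown, so no column can be chosen and no bound stated.

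**3. What unequal capture would do to a comparison**

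With true risks p_I and p_C and capture c_I and c_C, the observed risk ratio is (p_I × c_I) / (p_C × c_C).

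- Equal true risk, capture 0.50 vs 0.25: 0.50 / 0.25 = 2.0, a false doubling.
- Equal true risk, capture 0.75 vs 0.25: 0.75 / 0.25 = 3.0.
- True risk ratio 2, capture 0.25 vs 0.50: 2 × 0.25 / 0.50 = 1.0, a real doubling hidden.
- Equal capture at any level, equal true risk: 1.0.

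Chance that the false doubling reaches two-sided p < 0.05 with 250 per arm and a true risk of 10% in both arms: observed risks are 5.0% and 2.5%, difference 0.025. The pooled standard error is √(2 × 0.0375 × 0.9625 / 250) = 0.0170 and the unpooled one is √((0.05 × 0.95 + 0.025 × 0.975) / 250) = 0.0170. Power = Φ((0.025 − 1.96 × 0.0170) / 0.0170) = Φ(−0.49) = 0.31. For the threefold case (7.5% vs 2.5%) it is 0.73. Over true risks of 5% to 20% the two cases span 0.18 to 0.57 and 0.43 to 0.96.

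**The case against.** The strongest reply is that the protocol never promises what is said to be missing. Its objectives concern effectiveness; no adverse event comparison or safety conclusion is planned; its remark on the safety of behavioural treatment, in the Introduction, rests on earlier literature. That stands. The point limits what may later be claimed and does not contradict a stated aim.

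A reader might infer that the trial can make no valid harm comparison at all. The documents do not support that. The harms most plausible here, namely worse child behaviour, quality of life or sleep, or more parental distress, are scored on the same schedule in both arms. They can be compared, subject to the expected 50% loss and to unblinded parent report. They do not replace a direct question, since they detect only shifts on pre-chosen scales.

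A reader might also infer that an event counts only if a parent volunteers it, or that the intervention arm must show an excess. Neither follows. The committee's trigger is that an event becomes known, which is wider and includes what staff learn in calls. The intervention-only prompts do not ask about adverse effects, and no section routes their answers to the committee, so the direction of any imbalance cannot be predicted.

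Finally, parents who quit without opening the next session miss the stopping question, but they are not beyond reach: if they respond at 4 months they still get the barriers and satisfaction scales. And the full protocol or the appendix of measures, neither shown, might hold an adverse event form. The statements that events are not monitored and that Table 2 covers all measures point the other way.

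**Conclusion.** The point holds in a limited form. Passive capture is a stated design choice, no listed measure asks either arm about adverse effects, and the occasions on which problems might surface are unequal in an open-label trial. Adverse event counts from this system would not be comparable between arms, and a low or zero count would not show safety.

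The size cannot be fixed from the documents. Under the assumed capture values, a zero count in 125 people is compatible with a true risk anywhere from 2.4% to 9.5%, and the observed risk ratio could be off by a factor of 2 or 3 upward, or could hide a real doubling. These figures show how sensitive a count is to capture; they do not estimate what will happen. No figure in the protocol is shown to be wrong, and the symmetric score comparisons are unaffected by this point. It is a cheap improvement worth making, not a flaw in the primary analysis.

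**What to change.** Add one identical item, yes/no plus free text, to the existing 4- and 8-month REDCap questionnaires in both arms, asking whether the child or parent had any adverse or unwanted effect since the last assessment. Send positive answers, and the stopping reasons given before Sessions 2 to 5, to the existing adverse events committee. Base the between-arm comparison on the common item, with the number who answered it as denominator, and list events learned by any other route separately so that none is lost from the report.

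Recruitment began in September 2016 (English) and May 2017 (French), so some participants may already be past an assessment. For them, or if the item cannot be added, the report should state that adverse event capture was passive, is not comparable by arm and supports no safety conclusion.

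Cost: an ethics amendment, one short question at two existing time points, and some reading for the committee. Minor non-specific complaints will be recorded, and the item covers only those who respond, which on the protocol's own assumption may be half of those enrolled.

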### Commercialization

If the BNBD intervention is found to be effective, to ensure its sustainability, the investigators anticipate commercialization of the BNBD intervention. The investigators will work to commercialize this program for a reasonable rate, so that all parents of children with insomnia can have access to this intervention.

The BNBD intervention is protected by a trademark registered under the Canadian Intellectual Property Office. The Industry Liaison and Innovation Office with Research Services at Dalhousie University has executed an interinstitutional agreement for the BNBD study, which outlines and governs intellectual property (IP) rights, commercialization, and confidentiality and publication agreements between Dalhousie University and the partnering institutions: the Hôpital Rivière-des-Prairies, the Hospital for Sick Children, McGill University, University of Alberta, University of British Columbia, Université de Montreal, University of Toronto, and Western University. The IP relating to the session content remain with Dalhousie University and are licensed for use to the industry partner. The IP relating to the proprietary platform used to host the internet-based BNBD Intervention remains the property of the industry partner. Any IP that is jointly developed throughout the commercialization process has shared ownership.

### Conclusions and Significance

This research addresses significant public health issues through knowledge creation and translation to achieve direct benefits for the health and well-being of Canadian children and parents. This study aligns with the recognized need to more rapidly transfer new scientific knowledge to improve patient care and population health and targets the validation of new treatment delivery models to increase availability of effective treatment resources. This research is novel for Canadian and international pediatric health services and has the potential to have a direct and significant impact both in Canada and abroad.

## Appendix

Multimedia Appendix 1 Description of Measures.

Multimedia Appendix 2 CONSORT-EHEALTH checklist (V 1.6.1).

## Abbreviations

BNBD: Better Nights, Better Days
CONSORT: Consolidated Standards of Reporting Trials
eHealth: electronic health
HRQ: health-related questionnaire
IP: intellectual property
MID: minimal important difference
RCI: reliable change index
RCT: randomized controlled trial
